## Methods

### Procedures for Aim 1

The timeline of activities completed in aim 1 is given in Multimedia Appendix 1. The first set of activities involved identifying the study neighborhoods and the small businesses and YPAOs in these neighborhoods. Next, focus groups were conducted, and a local advisory board was formed. The focus group data were used by the local advisory board to refine the alpha components of the intervention we previously developed to create a beta version that was tested in aim 2 (Multimedia Appendix 2 [69-76]).

#### Study Neighborhood Identification

We used a multistep process recommended for use in urban health research to identify 27 distinct neighborhoods in New Castle, Delaware (mainly Wilmington, the largest city in the state) meeting our inclusion criteria requiring a minority concentration greater than 50%, median household yearly income in the lower third of all neighborhoods in these areas, and a land use mix that is at least 30% residential and at least 15% retail/commercial [77]. From the pool of 27 neighborhoods meeting our inclusion criteria, 20 were randomly selected to participate in the pilot study of the beta-i. Pairs of neighborhoods separated by at least 0.5 miles constituted the randomization unit with 1 randomly assigned to the treatment and the other to the control (see *Interventions* section later in this paper for a description of the study arms). This helped reduce the risk of contamination.

#### Small Businesses and Youth Physical Activity Opportunities Identification

During November and December 2018, we identified all small businesses and YPAOs in the study neighborhoods using various approaches and sources we had used in previous studies (registries, internet/phone books, media, community tours, and community members) [52,67,68,78]. YPAOs were defined as programs and places available to the youth with components and amenities that typically involved physical activity [24-28,52,68]. Some examples of YPAOs we found were playgrounds, ballfields/courts, classes, sports leagues, and various types of structures (eg, jungle gym). These YPAOs were located mainly at parks, churches, and for-profit businesses, which is consistent with previous research [52,79]. We included school components (eg, athletics) because these are important YPAOs [80]. YPAOs not available to the public (eg, worksite exercise programs) or those not designed primarily for physical activity (eg, sidewalks/streets and stairs) were not included. A tracking system developed in our previous study will be used to detect new YPAOs that emerge and dissolve during the intervention [78]. The system involves monitoring local media and internet sources, canvassing neighborhoods, and obtaining feedback from YPAO providers. Follow-up procedures (eg, phone calls) will be carried out to confirm if a YPAO is actually new and baseline data on existing YPAOs will be referenced to quantify the emergence of new ones. The information obtained on YPAOs was and will be carefully reviewed to eliminate duplication.

#### Focus Groups

Focus groups allowed us to obtain unique perspectives from neighborhood stakeholders, which were used to refine alpha-i components to better meet the needs/resources of the treatment neighborhoods. Participants were asked to consider components, provide recommendations, and suggest modifications. We specifically looked for input on our strategy for increasing support for YPAOs, how to efficiently handle administrative tasks, promoting YPAO provider fund use, ways to reduce barriers to using YPAOs, and long-term sustainability.

Between January and March 2019, we conducted 9 focus groups and analyzed the data. Each focus group was comprised 6 to 8 members recruited from the 27 low-income, minority neighborhoods that had met our inclusion criteria as outlined above. Participation was solicited from small business owners (3 focus groups), YPAO providers (3 focus groups), and parents and guardians of the youth (3 focus groups), using our personal contacts, referrals, flyers, and ads in local publications. Incentives (eg, food/drink, $20 gift card) were used to encourage participation and all group sessions were held in one of the study neighborhoods. The number of groups we used was adequate for ensuring saturation, providing us with a comprehensive picture of the domains and helping achieve focus group goals [81,82].

Each focus group lasted about 90 min and was moderated by a research team member with extensive training in qualitative methodology. The moderator was assisted by a second scientist who documented focus group proceedings and other process data (eg, nonverbal behaviors) [83]. Using a focus group guide developed for this project, the moderator walked members through the topics to be covered and used probes to clarify select responses or solicit more detailed information [83]. Members were given a chance to ask questions to ensure they understood the process. At the end of each focus group, the team debriefed by reviewing notes and discussing particularly relevant areas (eg, presence of domineering members) [84,85]. Insights from the debriefing sessions were used to enhance the quality of the data by providing an explanation for areas that seemed ambiguous after all data were transcribed and coded. Each session was audiotaped with 2 electronic digital recorders for later transcription.

#### Preparation for Aim 2

The final activities that were completed in aim 1 involved the refinement of alpha-i components by the local advisory board, mainly using focus group and survey outcomes, and the formation of the beta-i. We also prepared for baseline data acquisition and developed the tracking mechanism that will be used to monitor donations to the fund and the distribution of donations. This will allow us to closely examine the cost of fund administration. We will be interested in the costs to solicit, maintain, and track donations, offer recognition (process and materials), identify YPAO providers, and distribute funds to YPAO providers. Information from donors and YPAO providers will include name, location, contact information, and a detailed description of the donation (given or received). Because donations could be monetary (US dollars) and nonmonetary (goods/services and time), we will use the Statement of Financial Accounting Standards 157, Fair Value Measurements guide, to properly determine the US dollar value of all donation types. By the end of May 2019, the development of the beta-i was complete.

### Procedures for Aim 2

The timeline of activities involved in aim 2 is presented in Multimedia Appendix 3. During May and June, we completed baseline assessments on small businesses and YPAOs. The beta-i and the control intervention will then be implemented from July 2019 to June 2020. Follow-up assessments, which will mirror baseline assessments, will be conducted from July to August 2020. The project completion date is set for the end of August 2020.

#### Business Surveys

We developed the small business policy survey to capture the presence and development of small business support for YPAOs [67]. Using a test-retest design, we found high reliability coefficients (all>.95) for questions about YPAOs (eg, number supported and type), other physical activity promotion policies, and business/owner characteristics. In-person surveys were completed by trained personnel with a randomly selected sample of 244 small business owners. If an owner was not available, a supervisor or manager was interviewed if they indicated having the knowledge to answer our questions. We attempted to gather detailed information about the business (eg, marketing budget), the owner (eg, sex), and involvement with neighborhood initiatives. They were asked if they supported YPAOs and the cost, location, and reason for each YPAO supported. In the follow-up surveys, we will also include a series of open-ended questions to elicit information about the intervention and for the control businesses, questions about possible exposure to beta-i components and if this had influenced their YPAO-supporting activities. A thematic analysis, similar to the process outlined for the focus groups, will be done to analyze these short answer questions.

#### Youth Physical Activity Opportunity Provider Surveys

In-person interviews were conducted by trained personnel with a randomly selected sample of 44 YPAO providers. Our reliable YPAO survey was used to gather detailed information on the YPAO including the number of youth participants, descriptions of all features and amenities, programmatic information (eg, fees, operating times, and sessions per week), personnel qualifications, and start-up and operating costs including how costs were covered [52]. If a small business providing a YPAO was selected for the survey, we completed the YPAO survey with them in addition to the small business survey.

#### Interventions

As stated previously, the treatment intervention (beta-i) will be a derivative of the alpha-i intervention components given in Multimedia Appendix 2. The control intervention is based on the finding that under normal circumstances, small business owners are seldom asked to provide support for specific initiatives in their neighborhood and they almost never receive educational material about the benefits of supporting neighborhood initiatives. Usually they are just made aware of organizations (eg, nonprofits) accepting donations [67]. In keeping with this *standard of practice*, small businesses in the control neighborhoods will be offered a minimal intervention with an opportunity to donate to a fund supporting YPAOs. This fund will be established at our institution for credibility and tracking purposes. However, donors to the control fund will not be able to select specific YPAOs to support, donate directly to their neighborhood, or receive recognition for their donations. In addition, the email messages they receive will not utilize a marketing strategy and only contain basic information for donating along with contact information if they have any questions. A local advisory board will not be formed, and liaisons will not be used in the control neighborhoods. Email distributions in the control neighborhoods will coincide with those made in the treatment neighborhoods. Donations to the control fund will be given to groups not operating in the study neighborhoods to further their mission to provide the youth with low-cost obesity treatment options, such as YPAOs. Provided in Multimedia Appendix 4 is a description of the interventions.

### Procedures for Aim 3

Data for aim 3 will be collected at baseline and follow-up as per the measures described under aim 2 as well as additional measures described below and used to address our aim 3 hypothesis. These additional measures will be conducted at baseline and follow-up.

#### The System for Observing Play and Recreation in Communities

The system for observing play and recreation in communities (SOPARC) will be used according to the established protocols to count the number of youths using public YPAOs [86,87]. Briefly, each public YPAO will be visited by a trained observer who will first locate and map the size, location, and boundaries of all potential areas for leisure-time physical activity (ie, target areas). Then they will perform scans (ie, observation sweeps moving from left to right) of the target areas to obtain the desired information (eg, number and age group). Separate scans will be conducted for females and males. All parks will be assessed at baseline and follow-up 4 times a day on 4 separate days. The daily observation periods will be 7 am to 9 am, 11 am to 1 pm, 3 pm to 5 pm, and 7 pm to 9 pm and the 4 days will consist of 3 weekdays and 1 weekend day. This number of observations is the minimum needed to obtain robust estimates of park user characteristics [87]. Target areas will be assessed during each observation period according to a pre-established order determined by randomization and counterbalancing. During periods of moderate to severe precipitation, observations will be postponed until a later date that corresponds to the cancelled day/time period.

#### Physical Activity Resource Assessment

Trained field coders will use the Physical Activity Resource Assessment (PARA) to conduct concise (10-30 min) audits of YPAOs where surveys and SOPARCs were completed. The PARA is a reliable (ρ >.77) instrument for assessing characteristics of publicly available physical activity resources including YPAO [50]. It will be used to gain further insight about the quantity and quality of YPAO amenities, features, and incivilities.

#### Training

Interviewers were trained according to the guidelines developed by The Gallop Organization [88]. Several procedures were used to assure the quality of data collected. Among these were attempts at participant maximization (eg, short introductions), refusal prevention and conversion training, and other quality control functions, such as maintenance of confidentiality, monitoring of interviewers’ work, and validation of surveys to ensure respondents had actually been surveyed. Because the number of contact attempts and the patterns of businesses/YPAO operation hours are key factors impacting response rates, 2 attempts were made during each of the following periods: weekday mornings, afternoons, and nights; weekend mornings and afternoons. For the SOPARC and PARA, 2 observers/raters participated in a training session where they were given detailed instructions on the techniques [50,86].

### Analysis

#### Process Evaluations

Process outcomes will inform us of intervention challenges and lessons learned. They will be derived from meeting minutes, debriefing sessions, study records (eg, budgets), small business surveys, YPAO provider reports, adult local advisory board member reports, liaisons, and study team evaluations. The primary process outcomes will be related to the local advisory board (eg, attendance), cost of fund administration and logistics of tracking donations and providing recognition, user satisfaction with donating methods, logistics of using electronic messaging (eg, span blockers), and recruitment/retention of liaisons. This information will be used to inform planning of future implementations of the intervention and when interpreting/discussing outcomes from this study.

#### Qualitative Data Analysis Plan

An iterative, 2-phase thematic analysis will be conducted to capture the meaning behind the transcribed text with an overall purpose of creating an increasingly sophisticated and rich description about small business involvement with YPAOs. First, researchers will review the transcribed documents to develop a familiarity with the text and search for the patterns and the themes that occur frequently in a single session or are common across sessions. The data will then be coded by identifying passages that exemplify key concepts or ideas related to the major patterns and themes. The use of multiple reviewers will help establish construct validity and interrater reliability of the coding scheme and identified codes. During the second phase, a computer-assisted qualitative data analysis program (NVivo qualitative data analysis software; QSR International Pty Ltd. Version 12, 2018) will be used to check the rigor of the manual coding, help organize the large volume of data, analyze data, and provide a means for generating reports. Qualitative data analysis is typically iterative, recursive, and dynamic; therefore, we will move between the manual and the electronic process until we are satisfied that the coding scheme and results are representative of the participants’ perspectives. Furthermore, themes identified will be compared with the extant literature on the topic to further validate the findings [89].

#### Cost Analysis

The detailed information collected about YPAOs will be used to estimate the relative contributions made by small businesses toward their total yearly costs. Total yearly costs will be defined as all costs in the cost model incurred for the YPAO during the past 12 months (Multimedia Appendix 5). No discount rate will be considered for this short period. Cost-effectiveness analyses will be used to describe the total yearly costs incurred by small businesses for supporting YPAOs relative to the number of youths utilizing the YPAOs. Both 1-way and multiple way sensitivity analyses will be performed to measure the robustness of the evaluation.

#### Power Analysis

Our power analysis was based on the percent change in the proportion of small businesses supporting YPAOs at baseline that subsequently provided support for YPAOs during the intervention. Data to construct the primary outcome will be derived from tracking donations and small business surveys. Power formulas accounted for experimental condition, number of neighborhoods, number of businesses/neighborhoods surveyed, variance estimates of the outcome measure from preliminary studies, and a conservative estimate of the intraclass correlation coefficient (ICC). In our previous research, a 27% versus 8.0% increase in support for community physical activity initiatives by small businesses not supporting them at baseline was observed in the treatment and the control neighborhoods, respectively [78]. On the basis of our previous experience conducting research in neighborhoods and our desire to develop a sufficiently rich and diverse dataset, we tested whether 10 neighborhoods per condition would also provide sufficient statistical power for our primary outcome. Thus, the final power model was based on 10 neighborhoods per condition, 10 small businesses nested in each neighborhood, a difference in proportions of 19 percentage points, and an ICC of 0.05. It was determined that having 10 neighborhoods per condition would give us a statistical power of 86% to yield a statistically significant result. In a previous study, we completed interviews at 66.2% (98/148) of the small businesses visited [67]. Of them, 30.4% (45/148) refused and interviews could not be completed with an eligible individual at 3.4% (5/148) of businesses. For the proposed study, we expect an average of 50 small businesses per neighborhood or 500 per condition. Therefore, we will obtain a random sample at baseline of 185 small businesses per condition and expect to complete a baseline survey at 66.2% (122/185) per condition. Of these 122, we expect a loss-to-follow-up of 15% to 17%, giving us 104 businesses per condition or ~10 per neighborhood. This will allow us to achieve our goal of interviewing no less than 20% of the eligible businesses and obtaining a representative sample [84].

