**Methods:**

The alpha-i will be refined using information from focus groups and surveys conducted with small business owners and managers, YPAO providers, and parents and guardians of the youths from low-income, predominantly minority neighborhoods. A cluster randomized controlled trial will then be conducted for 1 year to examine the effects of the refined intervention (beta-i) on small business support for YPAOs in 10 low-income, minority neighborhoods. The control group of neighborhoods (n=10) will be provided with a standard practice intervention. The primary outcome for aim 2 will be the percentage of small businesses not supporting YPAOs at baseline that subsequently provide support for YPAOs at follow-up. We also will consider the US dollar equivalent of all types of support (monetary, goods/services, and time) donated for YPAOs by small businesses. In addition, we will examine the impact of the increased small business support for YPAOs on YPAO utilization by the youth.

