### Objectives

In accordance with the socioecological model and established philanthropic principles, we developed an alpha version of an intervention (alpha-i) for increasing small businesses’ involvement with YPAOs. We are now poised to create a beta version (beta-i) and conduct a pilot study of its *impact* on small business support for YPAOs and *YPAO utilization by the youth* in low-income, minority neighborhoods. To meet this objective, we will complete the following specific aims and address the specified hypotheses.

*Aim 1:* Refine alpha-i components by conducting focus groups with small business owners, YPAO providers, and parents and guardians of the youth from low-income, predominantly minority neighborhoods. Results of the qualitative analysis will inform final tailoring of the intervention to create the beta-i that will be tested in aim 2.

*Aim 2:* Determine the effect of the beta-i on small business support for YPAOs by conducting a cluster randomized controlled trial with randomization at the neighborhood level. The intervention neighborhoods (n=10) will receive the beta-i, whereas the control neighborhoods (n=10) will be provided a standard practice intervention for a period of 1 year.

*Hypothesis 1:* The beta-i will result in a significantly greater increase in the percentage of small businesses providing support (eg, monetary donations) for YPAOs than a standard practice intervention.

*Hypothesis 2:* The US dollar equivalent of all types of support (monetary, goods/services, and time) donated for YPAOs by small businesses exposed to beta-i will be greater than that donated by small businesses exposed to the standard practice intervention.

*Aim 3:* Examine the impact of the increased small business support for YPAOs on YPAO utilization by the youth. The primary outcome will be the percent change in the number of youths participating in YPAOs from baseline to follow-up.

*Hypothesis 3:* The percent increase in youth participants from baseline to follow-up will be significantly greater at YPAOs in the treatment neighborhoods receiving support from small businesses than at YPAOs in the control neighborhoods.

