#### Approach to Analysis

Before developing statistical models, an examination of the univariate distribution of variables will be conducted (eg, scatter plots). Statistics, such as means or proportions, standard errors, ranges, and estimates of skewness and kurtosis will be derived for the overall samples and stratified by condition and characteristics of small businesses and YPAOs using SAS 9.4 and used as guidelines in the application of both bivariate and multivariate analyses [85]. Data transformation procedures (eg, logarithmic) may be applied to quantitative variables whose distribution shows considerable departure from normality. In the case of discrete variables, results will provide guidance in recoding these variables appropriately for statistical modeling. Graphical data will be developed to provide visual comparisons of changes across time between the 2 study conditions on key measures of small business involvement and YPAO utilization by the youth. The primary outcome will be examined using a mixed-model, nested logistic regression analysis of proportions where (1) businesses are nested in neighborhoods and (2) neighborhoods are treated as a nested random effect within treatment conditions. Generalized models will be used to explore potential mediators/moderators of outcomes. For example, a model will be constructed with experimental condition (treatment vs control), neighborhood variables (eg, median income), and business variables (eg, number of employees and years in business) as the independent variables and mean percent change in small businesses donating as the dependent variable. In another model, donation amounts equated to US dollars will be used as the dependent variable. To accommodate the complex nature of the research design, the SAS PROC GLIMMIX and SAS PROC MIXED (SAS, 2015) procedures will be used.

### Sample Size Determination for Aim 3

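### The aim 2 primary outcome is defined among baseline non-supporters in the abstract but among supporters in the power section, and the 86% power counts all followed businesses although only about 60% would be non-supporters

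*Protocol article*

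**What the plan says.** Three places in the protocol article describe the outcome for aim 2.

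- **Abstract, Methods.** The primary outcome is "the percentage of small businesses not supporting YPAOs at baseline that subsequently provide support for YPAOs at follow-up". This is a conversion rate among baseline non-supporters.
- **Methods, Power Analysis.** The basis for power is the "percent change in the proportion of small businesses supporting YPAOs at baseline that subsequently provided support for YPAOs during the intervention". Read as printed, this is a rate among baseline supporters.
- **Introduction, Objectives, Hypothesis 1.** The intervention is to give a "significantly greater increase in the percentage of small businesses providing support (eg, monetary donations) for YPAOs than a standard practice intervention". No baseline status is mentioned.

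The Power Analysis section takes its effect size from "a 27% versus 8.0% increase in support for community physical activity initiatives by small businesses not supporting them at baseline", seen in the team's previous research. Its final model uses "10 neighborhoods per condition, 10 small businesses nested in each neighborhood, a difference in proportions of 19 percentage points, and an ICC of 0.05", and it reports 86% power. The 10 businesses per neighborhood come from a random sample of 185 businesses per condition, of which 122 are expected to be surveyed at baseline and 104 retained. No step in that chain selects on baseline support. The Business Surveys section shows that support status is asked in the survey itself. The last paragraph of Background in the Introduction says that about 60% of small businesses did not support YPAOs in the team's preliminary study.

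**The concern.** Baseline supporters and baseline non-supporters are mutually exclusive groups, so the abstract and the Power Analysis section cannot both describe the primary outcome. Hypothesis 1, read literally, covers a third population, all businesses, in which a supporter who lapses would offset a new one. Approach to Analysis says how the primary outcome will be modeled but does not restate its denominator, so it does not resolve the conflict.

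Two things are at stake. First, the set of businesses entering the primary analysis should be fixed before follow-up data exist, and the article leaves it contradictory. Second, if the abstract's definition is the intended one, only non-supporters are analysable. The power calculation then pairs rates for non-supporters with a sample size that counts everyone followed.

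**Working it through.** **Inputs**

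- Power Analysis: 10 neighborhoods per condition, 10 businesses per neighborhood, 27% v 8.0%, ICC 0.05, stated power 86%.
- Power Analysis: 122 baseline surveys per condition, 15% to 17% loss, 104 followed.
- Introduction, Background: about 60% non-supporters.
- Assumed, because it is not stated: two-sided alpha 0.05 (critical value 1.96).

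**Formulas**

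- Design effect = 1 + (m − 1) × ICC, with m the analysable businesses per neighborhood.
- Effective n per arm = 10m / design effect.
- Unpooled z = |p1 − p2| / √{[p1(1 − p1) + p2(1 − p2)] / n}; power = Φ(z − 1.96).
- The pooled-variance and arcsine versions were run alongside.

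**Step 1: reproduce the stated 86% with m = 10**

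- Design effect = 1 + 9 × 0.05 = 1.45; effective n = 100 / 1.45 = 69.0.
- Variance sum = 0.27 × 0.73 + 0.08 × 0.92 = 0.1971 + 0.0736 = 0.2707.
- z = 0.19 / √(0.2707 / 69.0) = 3.03; power = Φ(1.07) = 85.8%.
- Pooled 84.3%, arcsine 86.2%.

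The 86% is therefore sound for 10 non-supporters per neighborhood.

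**Step 2: count the analysable businesses**

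- 10 × 0.60 = 6 per neighborhood. From 104 followed, 104 × 0.60 = 62.4 per condition, or 6.24 per neighborhood.

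**Step 3: power with m = 6**

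- Design effect = 1 + 5 × 0.05 = 1.25; effective n = 60 / 1.25 = 48.
- z = 0.19 / √(0.2707 / 48) = 2.53; power = Φ(0.57) = 71.6%.
- Pooled 69.4%, arcsine 72.0%.
- With 6.24 per neighborhood, the three methods give 70.7% to 73.3%.
- A noncentral t on 18 degrees of freedom gives 66.8%, against 81.8% for m = 10.

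**Step 4: sensitivity to the share of non-supporters** (10 followed per neighborhood)

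| Non-supporters | m | Design effect | Effective n per arm | Power, pooled to arcsine |
|---|---|---|---|---|
| 50% | 5 | 1.20 | 41.7 | 63% to 66% |
| 60% | 6 | 1.25 | 48.0 | 69% to 72% |
| 70% | 7 | 1.30 | 53.8 | 74% to 77% |
| 80% | 8 | 1.35 | 59.3 | 78% to 81% |

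**Step 5: what 10 non-supporters per neighborhood would have required**

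- Followed: 100 / 0.60 = 167 per condition, against 104.
- Baseline surveys: 167 / 0.85 = 196 to 167 / 0.83 = 201 per condition, against 122.

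**The case against.** The strongest reply is that the article defines the aim 2 primary outcome only once, in the abstract, and that the Power Analysis sentence has merely lost a negative. That is the likeliest explanation: the same paragraph takes its rates from non-supporters, and no one would power a retention outcome on 27% v 8% conversion. A reader might infer that the trial has a rival retention outcome, or three competing primary outcomes. The article does not support that. Hypothesis 1 is loosely worded and is not labeled the primary outcome, and the Power Analysis section itself uses the word increase for conversion among non-supporters. The phrase "mean percent change in small businesses donating as the dependent variable" in Approach to Analysis belongs to an example of exploratory mediator and moderator models, so it is not another primary definition.

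A reader might also compute power for net change in all businesses. With 40% supporting at baseline and none lapsing, conversion of 27% v 8% becomes 0.40 + 0.6 × 0.27 = 56.2% against 0.40 + 0.6 × 0.08 = 44.8%. That is 11.4 points, with power of about 27% on follow-up proportions. The arithmetic follows from those assumptions, but the article never calls this outcome primary, so it does not show that the 86% is wrong. Nor do the documents give lapse rates from which to argue that conversion and net change would point in opposite directions.

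The two time phrases, at follow-up and during the intervention, can be read together: support given from July 2019 to June 2020 and ascertained in July to August 2020 fits both.

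What the reply does not remove is the printed contradiction, the unrestricted wording of Hypothesis 1, and the denominator behind the power figure. Restoring the negative makes that last problem plain.

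**Conclusion.** The concern holds in limited form. As printed, the abstract and the Power Analysis section name opposite groups for the primary outcome, and Hypothesis 1 names neither. The probable intention is clear, so this is mainly a correction of wording, but it concerns the primary outcome and should be made before follow-up data exist. The correction also has a numerical consequence. For the non-supporter outcome, the sample described gives power of about 69% to 72% rather than 86%, and power stays below 86% for non-supporter shares from 50% to 80%.

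This rests on two-sided alpha of 0.05, an ICC of 0.05 held constant as the analysable cluster shrinks, even cluster sizes, and the preliminary-study figure of about 60%. The calculation behind 86% is not itself in error; it was applied to a count that includes businesses outside the denominator.

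**What to change.** 1. Use one definition throughout: among surveyed businesses reporting no YPAO support at baseline, the proportion providing any support over the 12-month intervention, ascertained at follow-up.
2. Correct the Power Analysis sentence to refer to businesses not supporting YPAOs at baseline.
3. Reword Hypothesis 1 to match, and list net change in all surveyed businesses, including lapses, as secondary.
4. Restate the power for the expected number of non-supporters per neighborhood, with the alpha level and sidedness given. The Results section reports 244 completed baseline surveys, so the actual number of non-supporters can be counted and used in place of the 60% assumption.

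The cost is wording in three places and one recalculation. No new data are needed, because baseline support status is already asked in the business survey. The drawback is that the stated power becomes less favourable. Recovering 86% would have needed about 167 followed businesses per condition at 60% non-supporters.
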